# Smartphone-based intervention for postpartum depressive symptoms (Smart-e-Moms): study protocol for a randomized controlled trial

**DOI:** 10.1186/s13063-024-08304-5

**Published:** 2024-07-10

**Keywords:** PPD, Baby blues, Peripartum mental health, IBI, CBT, Prevention, Smartphone-delivered

## Abstract

**Background:**

Postpartum depression constitutes a significant public health issue, with prevalence rates ranging between 8 and 19% in high-income nations. Nevertheless, numerous barriers, including time constraints, societal stigmatization, and feelings of shame, contribute to the limited utilization of healthcare services during the postpartum period. Digital interventions offer an opportunity to enhance care for women experiencing postpartum depressive symptoms.

**Methods:**

We will conduct a two-arm randomized controlled trial to assess the effectiveness of a smartphone-based intervention in comparison to a treatment-as-usual control group in Germany. Our aim is to randomize 556 participants in a 1:1 ratio. Participants in the intervention group will be provided access to a preventive smartphone-based intervention called “Smart-e-Moms,” which incorporates therapeutic support and comprises 10 concise modules rooted in cognitive-behavioral therapy. For the intervention group, evaluations will take place at baseline (t0), prior to sessions 4 and 8 (intermediate assessments), and upon completing the intervention 6 weeks after baseline (t1). The control group’s assessments will be at baseline (t0) and 6 weeks after baseline. Follow-up assessments are scheduled at 12 and 24 weeks from baseline to examine the short-term stability of any observed effects. We anticipate that participants in the intervention group will exhibit improvements in their postpartum depressive symptoms (as measured with the Edinburgh Postnatal Depression Scale). Additionally, we will analyze secondary outcomes, including maternal bonding, stress levels, self-efficacy, satisfaction with the intervention, and healthcare utilization.

**Discussion:**

If Smart-e-Moms proves to be effective, it has the potential to play a significant role in postpartum depression care within German-speaking regions. Ideally, this intervention could not only benefit maternal well-being but also improve the prospects for healthy child development.

**Trial registration:**

German clinical trials registry DRKS00032324. Registered on January 26, 2024.

## Administrative information

Note: the numbers in curly brackets in this protocol refer to SPIRIT checklist item numbers. The order of the items has been modified to group similar items (see http://www.equator-network.org/reporting-guidelines/spirit-2013-statement-defining-standard-protocol-items-for-clinical-trials/).

## Introduction

### Background and rationale {6a}

Postpartum depression (PPD) is the most commonly observed mental health disorder in the postpartum period, with a prevalence of 8–19% of individuals in high-income countries, posing significant risks to both women and their infants [1–4]. PPD is a condition that can cause symptoms such as emotional numbness, depressed mood, ambivalent feelings towards the child, lack of energy, feelings of guilt or worthlessness, and even thoughts of self-harm. These symptoms can last for more than 2 weeks [5, 6].

PPD can have severe and long-lasting negative effects on the entire family if left untreated [7]. It affects the psychological well-being of mothers, their overall quality of life, and their interactions with their infants, partners, and family members [8]. Furthermore, it increases the risk of recurrent depressive episodes [9]. Severe or chronic depression in mothers can also increase the risk of impaired child development. For example, PPD in mothers has been associated with an increased likelihood of behavioral problems and mental health problems in their children [9, 10].

Several treatment methods have been proven to be effective and feasible for women with PPD [2]. Among evidence-based treatment options, cognitive-behavioral therapy (CBT) has been shown to be the most effective (Branquinho et al., 2021b). However, despite the essential need for detection and treatment of PPD to prevent harmful consequences [8], the majority of women with PPD remain untreated [11]. The large discrepancy between the prevalence of PPD symptoms and treatment utilization is striking: only around 15% of women with PPD symptoms receive professional help, while healthcare utilization among those who have already tested positive for PPD is estimated at 22% [12]. Due to several barriers, women seem to be less likely to seek preventive care services and treatment for PPD in the postpartum period and therefore underutilize mental health services [13].

These barriers primarily include structural barriers, such as lack of time, inflexible scheduling, and difficulties with childcare [14, 15]. In addition, limited knowledge, societal stigma, and feelings of shame and guilt contribute to the low rates of detection and to the lack of treatment [13, 14, 16, 17 ]. Consequently, many women with PPD fail to access appropriate care despite experiencing significant distress and suffering. Additionally, there is a shortage of accessible prevention and care services for mothers with newborns [18].

To address these structural, societal, and individual barriers, internet-based interventions (IBIs) have emerged as a recognized and easily accessible means of providing specialized therapeutic care to women with the potential to both prevent and treat postpartum depressive symptoms [19–21]. IBIs targeting PPD commonly use evidence-based treatment elements, such as CBT techniques including behavioral activation and cognitive restructuring [22–24], psychoeducational components [24–26], and mindfulness and self-compassion practices [24, 27, 28].

Recent clinical trials have indicated that IBIs for women with PPD offer enhanced accessibility, improved treatment outcomes, and increased cost-effectiveness [28, 29]. IBIs offer anonymity, independence from location and time constraints, and can be tailored to individual needs [30, 31]. While international research supports the efficacy of IBIs for preventing and treating PPD, there is currently a lack of such digital care services specifically tailored for women in German-speaking countries [18]. In addition, many existing interventions are self-guided [22, 32]. However, research indicates that guided interventions have the potential to enhance effectiveness, adherence, and satisfaction with the intervention [33–35].

## Objectives {7}

We aim to develop a smartphone-based intervention for women with postpartum depressive symptoms and evaluate its effectiveness. The study focuses on mothers at risk for developing postpartum depression within the first 6 months after childbirth. The research questions addressed are as follows:Does the therapist-guided smartphone-based intervention, Smart-e-Moms, reduce depressive symptoms more effectively than treatment as usual (TAU)?Does the intervention result in lower stress, higher mother-infant bonding, and higher self-efficacy as compared to TAU?How do users rate the usability, satisfaction, and utilization of the smartphone-based intervention?Are there differences in healthcare service utilization between the intervention and TAU?

## Trial design {8}

We will conduct a parallel-group, two-arm randomized superiority trial, which compares the effectiveness of a smartphone-based intervention to a control group (treatment as usual, TAU) in Germany. This trial protocol is reported following the SPIRIT guidelines. The study has been registered in the German clinical trial register under https://www.drks.de/DRKS00032324. The protocol includes all items of the WHO Trial Registration Data Set. Participants will be randomly assigned to (a) the smartphone-based intervention (IG) or (b) treatment as usual (TAU). Randomization will follow a 1:1 allocation ratio, with sample size calculations suggesting a required sample of 556 (IG = 278; TAU = 278). For the intervention group (IG), assessments will take place at baseline (t0), before sessions 4 (t0_1) and 8 (t0_2) (intermediate measurements), and after completion of the intervention 6 weeks from baseline (t1). For the control group (TAU), assessments will take place at baseline (t0) and 6 weeks from baseline. Follow-up assessments will take place 12 weeks and 24 weeks from baseline to assess the short-term stability of any effects achieved.

## Methods: participants, interventions, and outcomes

### Study setting {9}

The study is jointly run by Freie Universität Berlin (FU Berlin) and Universitätsklinikum Hamburg-Eppendorf (UKE). FU Berlin will be responsible for data collection. Participants can download the DIRECT app on their personal smartphones and take part in the intervention and all assessments using the app. DIRECT is a digital research platform optimized for clinical psychology studies, which was developed at the Center of Mental Health and Digital Science of the FU Berlin and is continuously developed further. Referrals are made via social media, midwives, gynecologists, pediatricians, maternity hospitals, and participating health insurance providers.

### Eligibility criteria {10}

Inclusion criteria: Women between 6 weeks and 6 months after delivery with an elevated score of postpartum depressive symptomatology (EPDS ≥ 10, cutoff for clinically relevant depressive symptoms), without acute psychotic symptoms or acute suicidality may participate in the study after signing an informed consent form.

Exclusion criteria: No birth event in the last 6 months, acute psychotic and/or suicidal symptoms, insufficient knowledge of the German language, current psychotherapeutic treatment at the time of inclusion. There are no exclusion criteria regarding psychopharmacological treatment.

### Who will take informed consent? {26a}

Participating women will provide informed consent within the smartphone-delivered program.

### Additional consent provisions for collection and use of participant data and biological specimens {26b}

No biological specimens will be collected, and no secondary studies or analyses will utilize the data collected during the trial.

## Interventions

### Explanation for the choice of comparators {6b}

The control group can utilize standard care (treatment as usual, TAU) to determine the benefit of the intervention compared to routine care. However, due to the information provided during the study registration and by filling out the depression scale EPDS, it is assumed that the participants are better informed about PPD and their own vulnerability. Therefore, an informed standard care TAU is assumed. This group will be asked to provide information about well-being and maternal bonding at comparable time points. For both the intervention and control groups, participants are excluded if they have regular appointments with a psychotherapist at the time of inclusion. However, participants are allowed to reach out to any psychotherapeutic or psychiatric help available via routine care at their own discretion during the intervention. This approach was chosen to assess the additional benefit of the intervention as precisely as possible in a naturalistic setting.

### Intervention description {11a}

Smart-e-Moms is a therapist-guided smartphone-based intervention to reduce symptoms of postpartum depression in mothers. The intervention will be delivered on the DIRECT app developed by Freie Universität Berlin. At the beginning of the intervention, each participant will be assigned to a therapist who guides the participant through the intervention and provides written, individualized feedback at several time points. Smart-e-Moms consists of 10 sessions (see Table 1 for a description of the intervention components) that are delivered to the participants over the course of 5 weeks (i.e., 2 sessions/week). Every session lasts about 20 min and consists of psychoeducational content, interactive exercises, and summaries of the modules. The sessions are presented sequentially to the participants, with individualized feedback and encouragement given by the therapist after sessions 1, 3, 5, 7, 9, and 10. Additional information on topics related to postpartum mental health (i.e., depression and breastfeeding, child development) will be available throughout the intervention. Furthermore, throughout the intervention, participants will gain access to several additional tools, including a mood tracker, an activity planner, relaxation exercises, exercises for strengthening maternal bonding, and a pinboard to collect moments of happiness.

**Table 1 Tab1:** Intervention components

Session number	Session name	Main topics	Key interventions	Session goal
1	Welcome session	Introduction of the intervention and individual goal setting, psychoeducation about PPD	Mood tracker^a^, expressive writing	Increasing the awareness of one’s own symptoms and normalizing negative emotions, establishing program motivation
Individualized written feedback provided by a psychologist				
2 + 3	Myths about motherhood	Myths about motherhood, association between thoughts and feelings	Collection of happy moments^a^, expressive writing	Debunking myths about motherhood through cognitive restructuring, reducing feelings of shame, increasing one’s focus on moments of happiness
Individualized written feedback provided by a psychologist				
4 + 5	Establishing soothing activities	Link between soothing activities and mood, dealing with challenges	Activity planner^a^, expressive writing	Behavioral activation and implementation of soothing activities—appropriate for the postpartum period—into everyday life with child
Individualized written feedback provided by a psychologist				
6 + 7	Stress management	Dealing with stress, psychoeducation on a mother’s need for self-care	Mindfulness and compassion-based exercises^a^, expressive writing	Dealing with stressful situations, integrating mindfulness practices and self-care into everyday life, increasing self-acceptance and self-compassion
Individualized written feedback provided by a psychologist				
8 + 9	Relationship to the child	Challenges in the mother–child relationship	Mindfulness exercises and playful activities for mother and child^a^, expressive writing	Normalizing ambivalent feelings, strengthening the mother–child relationship
Individualized written feedback provided by a psychologist				
10	Closing session	Summarizing key lessons learned from the intervention and introduction of strategies to maintain positive effects	Expressive writing	Maintaining positive changes, preventing relapse
Individualized written feedback provided by a psychologist				

^a^These functions are available to users throughout the intervention from the time of introduction

The unique aspect of Smart-e-Moms is its participatory development, ensuring that the app is specifically tailored to the needs of postpartum women. For instance, audio recordings of women sharing their experiences with PPD are integrated throughout the intervention to normalize users’ experiences and provide reassurance that they are not alone. Moreover, Smart-e-Moms offers continuous support from a psychologist, providing individualized feedback and encouragement throughout the intervention. The psychologists will be trained psychotherapists and/or psychotherapists in training working under the supervision of a trained and experienced psychotherapist. All participating clinicians will receive technical training and learn how to deliver individualized feedback to participants. In addition to the individualized guidance, Smart-e-Moms combines a comprehensive set of psychotherapeutic elements (e.g., CBT-tools, expressive writing, psychoeducation, mindfulness exercises), which distinguishes Smart-e-Moms from other German IBIs for perinatal women without guidance (Mind:Pregnany; [36]), or those focusing on informing about PPD [37]. Moreover, other German IBIs for perinatal women are not specifically tailored to the postpartum period (Mind:Pregnany,[36],I-PREGNO; [38]). A detailed overview of the intervention can be found in Table 1.

The therapists will be trained psychotherapists and/or psychotherapists in training working under the supervision of a qualified psychotherapist. All participating clinicians will receive technical training and learn how to deliver individualized feedback to participants. A detailed overview can be found in Table 1.

### Criteria for discontinuing or modifying allocated interventions {11b}

Participants can leave the study at any time for any reason if they wish to do so without any consequences.

Engagement in the program (i.e., starting and/or completion of sessions) will be automatically logged. After 1 week without starting or completing a new session, participants will receive a reminder message. Participants will still be invited to fill out all assessments even if they discontinue working on the sessions.

### Strategies to improve adherence to interventions {11c}

By nature, the intervention is highly manualized and standardized. All therapists will receive a manual and comprehensive training for using the app and delivering individualized feedback to the participants. To enhance the therapists’ training and ensure adherence of the participants, treatment will be closely monitored by a supervisor.

Engagement by the participants will be automatically logged and monitored by the therapists. Their weekly, individualized feedback messages are focused on encouraging the participants to continue working on the sessions. Participants receive push-up notifications in the app whenever individualized feedback by the therapist, a new session, or an assessment is available to them. To ensure engagement in the follow-up assessments, participants in both the intervention and the TAU group will receive monetary compensation with slightly higher compensations for the TAU group.

### Relevant concomitant care permitted or prohibited during the trial {11d}

For both the intervention and TAU groups, participants are excluded if they have regular appointments with a psychotherapist at the time of inclusion. However, participants are allowed to reach out to any psychotherapeutic or psychiatric help available via routine care during the intervention at their own discretion. We will assess medication use and additional health care utilization to analyze potential differences in the utilization of health services between the groups. This approach was chosen to assess the additional benefit of the intervention as precisely as possible in a naturalistic setting.

### Provisions for post-trial care {30}

N/a: There is no ancillary post-trial care or compensation. All participants in both the control group and the intervention group will be monitored throughout the whole follow-up period and can contact the study team. In case of crisis or suicidality, they will be offered a personal call by a trained psychotherapist.

### Outcomes {12}

#### Primary outcome measures

Edinburgh Postpartum Depression Scale (EPDS, [39]).

The primary outcome of the intervention will be the reduction of postpartum depressive symptoms, as measured by the Edinburgh Postpartum Depression Scale [39]. The self-report questionnaire consists of 10 items which are rated from 0 to 3 and summed to determine the overall score. A score of 9.5 or above is indicative of probable depression. The EPDS includes one item to assess suicidal ideation and self-harm tendencies that will be used to monitor potential self-harm throughout the intervention. The EPDS has demonstrated satisfactory validity and reliability and is the most commonly used outcome measure to assess postpartum depression. The German version of the EPDS has good psychometric properties [40]. The mean change from baseline will be compared between the intervention and the control group at post-assessment (t1), which is the most relevant time point of interest, and at follow-ups 1 and 2.

#### Secondary outcome measures

All secondary outcome measures have shown satisfactory reliability and validity in previous studies.

#### Postpartum Bonding Questionnaire [41]

Mother-infant bonding will be assessed with the Postpartum Bonding Questionnaire. It is a 16-item self-report scale with a rating from 0 to 5. The total score can be between 0 and 80, with a lower score indicating a better mother-infant bond. According to Brockington’s factor solution, 3 subscales are proposed: impaired bonding with a threshold of 12, rejection and anger with a threshold of 17, and threatened rejection with a range from 13 to 16. These scales showed an internal consistency of *α* = 0.85 of the German questionnaire. The mean change from baseline will be compared between the intervention and the control group at post-assessment (t1), which is the most relevant time point of interest, and at follow-ups 1 and 2.

#### General Self-Efficacy Scale [42]

This 10-item self-report scale assesses self-efficacy. Items are rated between 1 and 4 which results in an overall score between 10 and 40. Internal consistency varies in German samples between a Cronbach’s alpha between 0.89 und 0.94 [43]. The mean change from baseline will be compared between the intervention and the control group at post-assessment (t1), which is the most relevant time point of interest, and at follow-ups 1 and 2.

#### 1-Item Perkhofer Stress Scale [44]

Stress will be assessed with the 1-item Perkhofer Stress Scale, which is a combination of the Visual Analogue Scale and the Figure Rating Scale [44]. It consists of a horizontal line, with the left end representing no stress and the right end representing the greatest stress. Below the line, 6 emojis depict smiling faces at different levels. The scale shows satisfactory psychometric properties. The mean change from baseline will be compared between the intervention and the control group at post-assessment (t1), which is the most relevant time point of interest, and at follow-ups 1 and 2.

#### Questionnaire for the Assessment of Medical and non-Medical Resource Utilisation in Mental Disorders [45]

The FIMPsy can be used to assess the utilization of health care services in patients with mental disorders and thereby facilitate economic evaluations. We will use a selection of items and adapt them specifically for our target group.

The mean utilization score will be compared between the intervention and the control group at post-assessment (t1), which is the most relevant time point of interest, and at follow-ups 1 and 2.

#### Other measures

Other measures include sociodemographic, clinical, and pregnancy-related variables. Symptoms of birth-related post-traumatic stress disorder (PTSD) will be assessed with the City Birth Trauma Scale [46]. To record adverse childhood experiences the Childhood Trauma Screener [47] will be used.

The User Version of the Mobile Application Rating Scale (uMARS, [48]) will be used by end-users to assess the quality of mHealth apps. The uMARS consists of four objective quality subscales (engagement, functionality, aesthetics, information) and one subjective quality subscale (20 items in total). An additional subscale measures the perceived impact of the evaluated app (6 items). All items are measured on a 5-point scale. The uMARS showed excellent internal consistency (*α* = 0.90). Mean scores will be used to assess usability at post-assessment (t1).

Expectations before treatment will be assessed as a potential moderator with the Patient Questionnaire on Therapy Expectation and Evaluation [49] which consists of 11 items. Furthermore, we will use an IBI-adapted version of the 12-item Working Alliance Inventory [50] to assess the therapeutic alliance as a potential moderator.

### Participant timeline {13}

Figure 1 depicts the CONSORT flow diagram. Potential participants are directed to a landing page that provides information about the trial. After downloading the DIRECT app and creating an account for the intervention, participants give electronic informed consent and provide their contact information (mail and phone number). Afterwards, participants fill out a screening questionnaire to make sure they fulfill the inclusion criteria. In case participants screen positive for suicidality or psychotic symptoms, a follow-up call will be made by a trained psychotherapist to assess eligibility using the corresponding modules of the Mini International Neuropsychiatric Interview [51] and the Structured Clinical Interview for DSM-5 [52]. Participants eligible for inclusion will complete the baseline assessment (t0) and are randomized to either the intervention group (IG) or the control group (TAU). Both groups receive invitations to fill out the assessments after the completion of the intervention (IG), or at 6 weeks (TAU) (t1), 12 weeks (t2), and 6 months (t3) after allocation.

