## Data collection and management

### Plans for assessment and collection of outcomes {18a}

Our study focuses on postpartum depressive symptoms as the primary outcome, with secondary measures including mother–child bonding, self-efficacy, stress, app quality, and healthcare utilization. Other measures encompass sociodemographic, clinical, and pregnancy-related variables. Outcomes will be measured by self-reported questionnaires, which are assessed at baseline (t0), after completion of the intervention 6 weeks after allocation (IG) or 6 weeks after allocation (TAU) (t1), and at 12 weeks (t2) and 6 months (t3) after allocation. Participants who receive the intervention will also complete an intermediate assessment before session 4 (t0_1) and session 8 (t0_2). All questionnaires will be presented via the DIRECT app that also hosts the intervention. A detailed overview of all assessments can be found in Table 2.

**Table 2 Tab2:** Schedule of enrolment, interventions, and assessments

**Time point**		**Study period**							
		**Enrollment**	**Baseline**	**Allocation**	**Post-allocation**				
		(− t1)	(t0)	(0)	(t0_1) Session 4, ~ week 2	(t0_2) Session 8, ~ week 4	(t1) After completion, ~ week 6	(t2) Follow-up, week 12	(t3) Follow-up, week 24

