### Plans to promote participant retention and complete follow-up {18b}

Participants will receive push-up notifications that questionnaires are available in the app and will be reminded once if they do not complete the assessment. Participants who discontinue working on the sessions will still be invited to participate in the assessments. They will receive a monetary incentive to complete assessments. Participants in the intervention group will receive €15 for completing the 3-month follow-up assessment and an additional €25 for completing the 6-month follow-up assessment. Participants in the TAU group will receive €15 for completing the 6-week post-intervention assessment, an additional €15 for completing the 3-month follow-up assessment, and an additional €45 for completing the 6-month follow-up assessment.

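### The key assessment t1 is defined inconsistently for the intervention arm: triggered by completing the programme in one place, placed at week 6 in others

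*Protocol article*

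**What the plan says.** **Timing of t1.** The participant timeline {13} sends the assessments "after the completion of the intervention (IG), or at 6 weeks (TAU) (t1), 12 weeks (t2), and 6 months (t3) after allocation". Here IG has an event and no week, and TAU has a week. The schedule in Table 2 labels the column "t1) After completion, ~ week 6", while its t2 and t3 columns carry plain week numbers. Three other places give IG both an event and a date: the abstract ("upon completing the intervention 6 weeks after baseline (t1"), the trial design {8} ("after completion of the intervention 6 weeks from baseline (t1") and the text of {18a} ("after completion of the intervention 6 weeks after allocation (IG) or 6 weeks after allocation (TAU) (t1"). For TAU, {8} says that "assessments will take place at baseline (t0) and 6 weeks from baseline".

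**Programme and non-completers.** Section {11a} plans ten sessions over 5 weeks, two per week. Section {11b} sends a reminder after a week of inactivity and keeps inviting women who stop the sessions to every assessment.

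**Role of t1.** Section {12} names t1 as the time point that matters most for the EPDS comparison. Section {20a} compares the arms at t1, t2 and t3 in all randomised women.

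**Payment.** Section {18b} states: "Participants in the TAU group will receive €15 for completing the 6-week post-intervention assessment". It then gives TAU EUR 15 at 3 months and EUR 45 at 6 months. IG gets EUR 15 and EUR 25 at those two points, and nothing is listed for t1. Section {11c} describes this as compensation "with slightly higher compensations for the TAU group".

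**The concern.** In a parallel-group comparison of change from baseline, both arms should be measured at the same time since allocation. Depressive symptoms after childbirth may change without treatment, so a difference in elapsed time can appear as a treatment difference. If IG is measured on completion, fast users answer before week 6, slow users after it, and women who never finish have no date.

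That last group matters for both planned analyses. The intention-to-treat comparison includes them. The as-treated comparison moves IG women who did not use the app into the control group, and those women can never complete.

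The payment difference is a separate and smaller matter. It can make response at t1 differ by arm, in an unblinded trial with self-reported outcomes and a planned dropout of 50% over 6 months.

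**Working it through.** **1. The statements side by side**

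| Place | IG t1 | TAU t1 | Anchor |
|---|---|---|---|
| Abstract | completion, 6 weeks | 6 weeks | baseline |
| Trial design {8} | completion, 6 weeks | 6 weeks | baseline |
| Participant timeline {13} | completion, no week | 6 weeks | allocation |
| {18a}, text | completion, 6 weeks | 6 weeks | allocation |
| Table 2 | completion, about week 6 | same column | not stated |

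All five tie IG's t1 to completion. Three also fix it at 6 weeks, one makes the week approximate and one gives none. A woman on the planned pace finishes at week 5, one who falls behind finishes later, and one who stops never finishes. Completion and week 6 are therefore different rules, and the text does not say which governs.

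The last follow-up is also labelled in two ways: 24 weeks in the abstract, {8} and Table 2, and 6 months in {13}, {14}, {18a} and {18b}. Six months is about 52/2 = 26 weeks, so the labels differ by about 2 weeks.

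**2. The plan's own figure, for scale**

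Inputs from {14}: d = 0.3, one-sided 5%, power 0.80, 50% dropout. The exact one-sided t-test needs 138.07, so 139 per arm, with power 0.802 at 139. Then 2 x 139 = 278 and 278 / (1 - 0.5) = 556. Both stated figures reproduce. They are set on t3 and do not depend on when t1 is taken.

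**3. What a timing gap could do (assumptions, not document figures)**

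The protocol gives no symptom slope and no completion times. Let r be the untreated decline in EPDS in SD per week, and g the mean number of weeks by which IG's t1 falls after TAU's. The bias in d is r x g, positive in favour of IG. Assume r from 0.02 to 0.10.

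| Mean gap g | Bias in d | Share of 0.3 |
|---|---|---|
| -1 week (IG at week 5) | -0.02 to -0.10 | -7% to -33% |
| 0 (t1 fixed at week 6) | 0 | 0% |
| +2 weeks | +0.04 to +0.20 | 13% to 67% |

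With no true effect and 139 per arm, the one-sided error is 1 - Phi(1.645 - bias / sqrt(2/139)), where sqrt(2/139) = 0.120. A bias of 0.04 gives about 9.5%, and 0.20 gives about 51%. In the early case the error falls below 5% and a real effect is understated.

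**4. Payment**

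IG: 0 + 15 + 25 = EUR 40. TAU: 15 + 15 + 45 = EUR 75. The ratio is 75/40 = 1.875, so TAU is paid 88% more.

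Assume that t1 response is 10 to 20 points higher in TAU, and that non-responders score 0.2 to 0.4 SD worse than responders in both arms. A complete-case contrast then shifts by (difference in response) x (difference in score): 0.10 x 0.2 = 0.02 to 0.20 x 0.4 = 0.08 SD in favour of IG, or 7% to 27% of 0.3. The full information maximum likelihood analysis in {20c}, with baseline variables as auxiliaries, would remove the part explained by observed variables.

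**The case against.** The best defence on timing is that three places put IG's t1 at 6 weeks and Table 2 says about week 6. Only the timeline sentence omits the week, and it may simply be condensed. Read that way, both arms are measured together, the timing bias is zero, and women who stop the sessions have a date. A journal article may also leave exact triggers and response windows to the full protocol. In addition, t2 and t3 are set by the calendar in both arms, so only one of three comparisons is exposed.

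Much of this stands, and it limits the point to an inconsistency. It does not remove it. The three passages still attach completion to the date, {13} gives the arms different rules in one sentence, and the affected time point is the one that the protocol ranks first. Conflicting published definitions are not the same as detail left elsewhere.

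On payment, {11c} discloses the difference and gives its purpose, engagement with follow-up. TAU women receive no app and no therapist feedback, so paying them more may reduce differential response, and equal payment might increase it. Payment is not part of the treatment contrast and acts only through missing data. That stands, so equal payment cannot be demanded on these documents. What does not stand is the description of an 88% difference as slight.

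**Conclusion.** The point holds as an inconsistency in the definition of t1 for IG. Followed as written, the timeline in {13} gives arm-dependent timing and no t1 date for non-completers. Followed as the abstract, {8} and the text of {18a} can be read, t1 is at week 6 in both arms and there is no timing bias. Under a completion trigger, the assumed slopes and gaps give anything from -0.10 to +0.20 SD. Neither sign nor size can be taken from the documents.

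A reader might infer more: that IG's t1 is definitely triggered by completion, and that the app is therefore credited with natural recovery. The documents support neither. The trigger is unresolved, and a woman on the planned 5-week pace would answer early, which works against the app.

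A reader might also infer that unequal payment by itself biases the t1 contrast, or that t1 is the only assessment unpaid in IG. No response rates by arm are given, so the first is conjecture. On the second, {18b} lists no payment for baseline or the two intermediate assessments either. What is true is that t1 is the only post-treatment assessment paid in one arm alone.

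**What to change.** **Main change.** In {13}, {18a} and Table 2, state that t1 is sent 6 weeks after allocation in both arms, regardless of sessions completed, with one common response window. Bring the abstract and {8} into line. Use one anchor throughout (baseline or allocation) and one label for t3 (24 weeks or 6 months).

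The cost is an app setting and protocol wording. This version precedes the planned first enrolment, and unequal timing could not be undone once data are collected. The small downside is that some IG women will answer t1 before finishing all sessions.

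**Secondary change.** Correct the description of the payments in {11c} and give the reason for the t1 difference. Report t1 response by arm, and add a sensitivity analysis for data not missing at random, for example by shifting the unobserved t1 scores over a stated range. This costs text and one extra analysis, and no new sample size follows.

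**Optional.** Payment could be equalised. Raising IG to the TAU level costs at most (75 - 40) x 278 = EUR 9,730. A budget-neutral split is (40 + 75) / 2 = EUR 57.50 per woman, which gives up the extra retention incentive in TAU.
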